### Participant timeline {13}

#### Study calendar

Duration of the inclusion and randomization period: 36 months.

Duration of follow-up by patient: 12 months (± 30 days) after transplantation (36 months maximum).

Total duration of the study: 48 months (± 30 days).

Start of inclusions: September 2019.

#### Conduct of the study

The overall schedule and time commitment for trial participants are summarized in Table 1.

**Table 1 Tab1:** Schedule of enrolment, interventions, and assessments in the HOPExt trial

Stages	V1 screening	V2 inclusion		V3	V4	V5–V11	V12	V13–V16
Time point	At inscription for LT or at pre-LT visit	D0 At hospitalization for LT	D0 HOPE group only	D0 + 6h (+/-2h) after LT	D0 + 12h (+/-2h) after LT	Day 1 to day 7 (+/-1day)	End of hospital stay	M3; M6: M9 and M12 (+/-30 days)
Actions								
Inclusion/non-inclusion criteria	X	X						
Informed consent	X							
Medical history and patient characteristics^1^	X							
MELD score	X At inscription	X						
Randomization^2^		X						
Clinical examination^3^		X					X	X
Biological analyses^4^		X (before LT)		X	X	X	X	X
Child–Pugh score		X (before LT)						
Donor characteristics^5^		X						
HOPE perfusion parameters^6^			X					
Bacteriological and fungal analyses^7^		X	X					
Intra-operative data^8^		X						
Liver biopsy^9^		X both groups	X					
Machine perfusate sample^10^			X					
ICU and hospital stay							X	
Morbidity (Clavien–Dindo score, CCI)							X	X At M3 only
Concomitant medication		X		X	X	X	X	X
Adverse events		X		X	X	X	X	X
Abdominal contrast enhanced MRI/MRCP								X At M12 only

^1^Patient characteristics: age, gender, height, weight, BMI, blood group, cause of cirrhosis, indication for transplantation, medical history (diabetes mellitus, arterial hypertension, transjugular intrahepatic portosystemic shunt), pretransplant status of residence (home, hospital ward or intensive care unit (ICU))

^2^Randomization will be performed after the harvesting team has macroscopically assessed the graft and confirmed that the graft will be harvested. After checking the inclusion and non-inclusion criteria, an online randomization tool will be used. Randomization will be stratified by center and MELD score at the time of transplantation with a cut-off of 30

^3^Clinical examination: vital signs (temperature, blood pressure, heart rate), body weight, height, BMI

^4^Biological analyses: AST, ALT, GGT, alkaline phosphatase, bilirubin, factor V, INR, platelets, creatinine, GFR, lactates. At V2 only, a pregnancy test (beta HCG) will be done for women of childbearing age

^5^Donor characteristics**:** age, gender, height, weight, BMI, blood group, length of stay in intensive care unit, cause of death, occurrence of cardiac arrest, biological test (AST, ALT, natremia)

^6^Parameters measured during HOPE perfusion (only in HOPE group): perfusion pressure, flow, temperature, duration of machine perfusion, perfusate oxygenation (partial pressure O2), and CO2 content (partial pressure CO2) at the beginning and at the end of machine perfusion; perfusate AST and ALT, LDH, hyaluronic acid, lactate levels at 30 min, and at the end of machine perfusion

^7^Bacteriological and fungal samplings will be taken on static storage solution (IGL-1) at the end of the back-table in both groups and of the perfusion solution at the end of machine perfusion for HOPE group

^8^Intra-operative data: surgical technique of transplantation (piggy-back vs. vena cava resection), length of procedure, transfusion needs (fresh frozen plasma, red blood cell, thrombocyte concentrate), occurrence of post-reperfusion syndrome (decrease of 50% of the median arterial pressure during the 5 min after the revascularization), cold ischemia time, circulatory support at the end of transplantation (noradrenaline (mg/h))

^9^A biopsy will be taken on the back-table before machine perfusion in both study groups, immediately after liver machine perfusion in the HOPE group, and after reperfusion of the liver in both groups

^10^3 ml sample will be taken from machine perfusion solution during HOPE perfusion (only in HOPE group), at 30 min and at the end of machine perfusion

#### Pre-screening

Patient eligible for liver transplantation after decision of the multidisciplinary board.

#### *Screening visit* = *V1*

All consecutive transplant candidates admitted to interdisciplinary transplant outpatient clinics requiring liver transplantation will be assessed for study eligibility by senior staff physicians (transplant surgeon). Patients on the waiting list for liver transplantation will be informed orally and in writing by a physician (transplant surgeon or hepatologist) about the study. Patients who are willing to participate, meet inclusion/non-inclusion criteria, and provide written informed consent will be included in the study.

Past medical history and patient characteristics will be collected: age, gender, height, weight, BMI, blood group, cause of cirrhosis, indication of transplantation, medical history (diabetes mellitus, arterial hypertension, transjugular intrahepatic portosystemic shunt), and pretransplant status of residence (home, hospital ward or ICU). The MELD score at inscription (INR, creatinine, bilirubin, and dialysis) is also recorded.

#### *Inclusion visit/randomization* = *V2*

#####  D0, visit 2

Verification that the consent form was signed by the patient and the investigator.

After the allocation and acceptance of the organs, the investigator will check the eligibility criteria. If the criteria are met, the liver recipient (study participant) will be randomized. The team of local investigators will be informed accordingly in order to set up the perfusion device. If the criteria are not respected, the patient will leave the study (premature termination of participation).

*Randomization*: it is important to note that absolutely no changes will be made to the national liver allocation rules. The study does not interfere or change the process of accepting or declining a liver offered to a certain patient in any way. Once a suitable recipient for the liver is identified, the recipient will be invited to come to the relevant transplant center for the surgical procedure as per routine procedure. Randomization will be performed after the allocation of the graft or after the harvesting team has macroscopically assessed the graft and confirmed that the graft will be harvested, according to the center practice. No study-related factors will be assessed before randomization. After checking the inclusion and non-inclusion criteria, an online randomization tool will be used. Randomization will be stratified by center and MELD score at the time of transplantation with a cut-off of 30.

*Prior to transplantation*: physical examination, vital signs, laboratory values (AST, ALT, GGT, alkaline phosphatase, bilirubin, factor V, INR, platelets, creatinine, GFR, lactates), MELD score (dialysis), CHILD–PUGH score (encephalopathy, ascites, albumin, prothrombin rate), and donor characteristics will be recorded. Concomitant medications and adverse events will be assessed.

*Liver transplantation*: back-table, recipient hepatectomy, and implantation will always be done by the principal investigator and sub-investigators. During recipient hepatectomy, the liver graft will be either stored in cold storage or perfused with the HOPE machine, according to the randomization. Parameters of the HOPE perfusion will be collected. Lot numbers of perfusate (Belzer-MPS) and perfusion device disposables will be recorded in the source document and eCRF.

In the control group, a biopsy of the liver graft will be taken at the beginning of the back-table preparation. Another biopsy will be taken after liver graft reperfusion in the recipient (routine practice).

In the experimental group, a biopsy of the liver graft will be taken at the beginning of the back-table preparation. Another biopsy will be taken at the end of the HOPE perfusion. A third biopsy will be taken after liver graft reperfusion in the recipient (routine practice). Study-related liver biopsies are (1) additional liver graft biopsy on the back-table in the control group and (2) additional liver graft biopsies before and after machine perfusion in the experimental group. Those biopsies are performed ex situ on the back-table without specific risk for the patient.

In order to look for any bacterial or fungal contamination during the whole process, samples of static storage solution (IGL in both groups) at the end of the back-table and samples of machine perfusion solution (Belzer-MPS) at the end of machine perfusion will be taken for bacteriological and fungal analyses. Those bacteriological and fungal samples will be analyzed by the microbiology laboratories of the participating centers in accordance with the European Pharmacopoeia 2.6.1 Sterility Analysis Protocol.

During surgery, intra-operative data are collected: surgical technique of transplantation (piggy-back vs. vena cava resection), length of procedure, transfusions needed (fresh frozen plasma, red blood cell, thrombocyte concentrate), occurrence of post-reperfusion syndrome (decrease of 50% of the median arterial pressure during the 5 min after the revascularization), cold ischemia time, and circulatory support at the end of transplantation (noradrenaline (mg/h)).

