### Who will take informed consent? {26a}

Patients will be informed during pre-transplantation consultations with a surgeon or a hepatologist prior to being placed on the waiting list for liver transplantation. For patients already on the waiting list, information could be made during a follow-up outpatient consultation. A time to think will be left to the patient. Once the patient has asked all questions concerning the study and agrees to participate in the study, consent will be signed by both the patient and the investigator.

Final inclusion and randomization will be done after accepting a liver graft that meets the ECD criteria.

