## Interventions

### Explanation for the choice of comparators {6b}

The standard French liver allocation rules will be followed. The study does not interfere or change the process of accepting or declining a liver graft offered to a patient in any way. If the liver is suitable for transplantation and all inclusion and exclusion criteria are met, the liver will be randomized to either HOPE after cold storage or static cold storage only. The control group will use the gold standard static cold storage technique (4 °C) with Institute George Lopez (IGL-1)® solution from graft harvesting until liver transplantation as routine practice in the eight centers.

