## Assignment of interventions: allocation

### Sequence generation {16a}

Randomization will be performed after the allocation of the graft or after the harvesting team has macroscopically assessed the graft, according to the center practice.

It will be stratified by center and MELD score at the time of transplantation, with a cut-off of 30 (MELD < 30 versus MELD ≥ 30).

The randomization process will be centralized and carried out via Ennov Clinical software. The randomization list will be drawn up by the methodologist/biostatistician of the Clinical Research Center at the Croix-Rousse University hospital, Lyon, France.

The randomization list will be kept for 25 years in a tamper-proof envelope with the mandatory information (signature of the person in charge of the list, date and version number, complete title, and code of the research protocol). This list will also be sent to the Clinical Research Center data manager for implementation in the Ennov Clinical software.

The investigator or a person designated by the principal investigator will randomize patients via the Ennov Clinical software. Only authorized persons will be able to perform the randomization. A confirmation email will be sent to the person who performed the randomization after each randomization, to the investigator associated with the patient, and to the management center.

In case of cancellation of the transplant for any reasons, the data manager will cancel the randomization. The patient will remain included in the study for randomization in one of the study arms.

The whole process (randomization, modifications, etc.) will be recorded in the audit trail of the study, which will be integrated in the clinical data management system (CDMS). This audit trail will be transmitted at the end of the study to be archived with all the study documents.

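### Centres may randomise at graft allocation, although Table 1 requires confirmed harvest first; in this open-label trial the early option discloses the arm before a decision that affects entry to the primary analysis set

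*Protocol article*

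**What the plan says.** The protocol article describes the moment of randomisation in several places.

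- **Table 1, footnote 2** (Conduct of the study) gives one time point: "Randomization will be performed after the harvesting team has macroscopically assessed the graft and confirmed that the graft will be harvested".
- **Inclusion visit/randomization = V2** gives two: "Randomization will be performed after the allocation of the graft or after the harvesting team has macroscopically assessed the graft and confirmed" that it will be harvested, depending on local practice.
- **Sequence generation {16a}** repeats the pair: "Randomization will be performed after the allocation of the graft or after the harvesting team has macroscopically assessed the graft, according to the center practice".
- **Who will take informed consent? {26a}** says: "Final inclusion and randomization will be done after accepting a liver graft that meets the ECD criteria".
- **Explanation for the choice of comparators {6b}** sets a precondition: "If the liver is suitable for transplantation and all inclusion and exclusion criteria are met, the liver will be randomized".

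On what is known beforehand, the V2 section says "After the allocation and acceptance of the organs, the investigator will check the eligibility criteria" and has the patient randomised if they are met. The same section also says "No study-related factors will be assessed before randomization".

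Randomisation is stratified by centre and by MELD at transplantation, cut at 30. Under Sequence generation {16a}, when a transplant is cancelled for whatever reason, the data manager cancels the randomisation and the patient stays available to be randomised to either arm. The full analysis set, which is the primary population, consists of randomised patients who were transplanted. The trial is open-label (Who will be blinded {17a}).

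**The concern.** Footnote 2 and the two running-text sections cannot all be followed. A centre that randomises at allocation complies with the text and breaches the table.

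The earlier option matters because of three other features of the design: the arm is not masked, the primary analysis set is defined by an event after randomisation (transplantation), and a cancelled transplant erases the allocation. If the arm is known before the graft has been inspected and harvest confirmed, people who know it may be involved while it is still open whether that patient will count in the analysis. Exclusions after randomisation that differ by arm are a selection problem, and no later analysis of the transplanted patients can fully repair it.

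Two related points are left open: which MELD value defines the stratum at an early-randomising centre, and what the sentence denying study-related assessment before randomisation is meant to say.

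**Working it through.** **1. Is the sample size affected?** The protocol attaches no figure to the timing, so I checked only whether its sample size depends on it. Inputs from Sample size {14}: EAD 30% against 15%, two-sided alpha 0.05, power 0.80, 10% dropout.

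- Arcsine effect size: h = 2·asin(√0.30) − 2·asin(√0.15) = 0.3639.
- n = 2·((1.960 + 0.842)/h)² ≈ 118.6, rounded up to 119 per group, as stated.
- 119/0.90 = 132.2, rounded up to 133 per group, 266 in total, as stated.

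Purely as an illustration with assumed loss rates c, suppose cancelled randomisations were never replaced. Power would be Φ(h·√(133(1 − c)/2) − 1.960): 84.3% at c = 0, 80.4% at 10% and 75.6% at 20%. Because the patient can be randomised again, this loss need not occur. The issue is selection, not numbers.

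**2. What separates the two time points?** At the later point the harvesting team has inspected the graft and harvest is confirmed. At the earlier point neither need have happened. Acceptance of the offer precedes both, since the V2 section places the eligibility check after acceptance.

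**3. Who knows the arm in between?** Under Sequence generation {16a} a confirmation email goes to the person who randomised, the patient's investigator and the management centre. Under the V2 section the local team is informed so that it can prepare the device. The documents do not say whether the harvesting team is told.

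**4. How does a decision in that interval reach the primary analysis?** If the graft is turned down at inspection and the transplant does not go ahead:

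- the randomisation is cancelled, so the first allocation no longer counts;
- the patient may be randomised again and may then receive the other arm;
- the first allocation contributes nothing to the full analysis set, because no transplant followed it.

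Under footnote 2 the same refusal happens before any allocation exists. The early option therefore moves one source of cancellations from before randomisation to after it.

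**5. Which MELD?** Table 1 provides two values: one at inscription (V1) and one at D0 (V2). The stratum calls for the score at transplantation. The V2 section lists the D0 laboratory values and MELD as pre-transplant items, after the randomisation paragraph, and has the recipient called in once identified as suitable. It does not say whether D0 results must be in hand, or which value to enter if they are not.

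**6. The sentence on study-related factors.** Taken literally, it excludes any such assessment before randomisation. The next sentences require the inclusion and non-inclusion criteria to be checked and the patient to be stratified by MELD. Both are study-related and both must come first.

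**The case against.** The strongest reply is that allocation is only the earliest permitted moment and that the eligibility check still comes first at every centre. The V2 section says so, and the consent and comparator sections agree. The protocol also states that the trial does not influence acceptance or refusal of a liver. This reply stands as far as it goes. It shows that the early option does not waive eligibility, but it offers no safeguard for decisions made once the arm is known.

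A reader might infer several stronger things that the documents do not support.

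- **That eligibility is necessarily verified on different information in different centres.** One donor criterion is enough, and six of the seven (age, intensive care stay, BMI, natremia, AST, ALT) are donor-record data that do not require harvest. Differing information is a possibility, not something the protocol states.
- **That biopsy-proven steatosis separates the two time points.** Macroscopic inspection is not a biopsy, and the scheduled study biopsies follow both points; for controls, "In the control group, a biopsy of the liver graft will be taken at the beginning of the back-table preparation".
- **That every patient later found ineligible leaves the primary analysis.** Such a patient who is nevertheless transplanted stays in the full analysis set. Only those not transplanted drop out.
- **That a number of lost patients can be given.** The documents do not say how many of the eight centres randomise at allocation or how often a transplant is then cancelled, and the re-randomisation rule means that such cases need not use up the dropout allowance.
- **That centre-specific timing by itself biases the comparison.** Randomisation is stratified by centre, so both arms share the local time point. That protects balance at randomisation, but not against arm-dependent decisions afterwards.

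The sentence on study-related factors may have been meant only to say that the trial does not interfere with allocation. Its context makes that plausible, but the sentence does not say it.

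**Conclusion.** The concern holds in a limited form and should be corrected. Three things are established from the text alone: footnote 2 conflicts with the V2 and sequence-generation sections on when to randomise; the MELD value for the stratum is not fixed for a centre that randomises before D0 results exist; and the sentence on study-related factors conflicts with the eligibility check and stratification beside it.

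The consequence for the comparison is a risk, not a demonstrated bias. It requires that at least one centre uses the early option, that someone who knows the arm can influence whether harvest or transplantation goes ahead, and that this influence differs between arms. The documents neither confirm nor exclude any of these, so no size can be given. The planned 119 and 133 per group are unaffected.

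The later time point would reduce exclusions after randomisation but not end them. The protocol itself foresees recipients found to be non-transplantable, and those cases may still arise after randomisation.

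**What to change.** 1. Use the footnote 2 time point in all centres. In the V2 section and in Sequence generation {16a}, delete the allocation alternative and the deferral to centre practice.
2. Make two entries mandatory in the web randomisation module before an arm is released: the donor criterion that qualifies the graft, and the MELD value used for the stratum, defined as the most recent value available at randomisation.
3. Reword the sentence on study-related factors so that it states what is intended, for example that no trial procedure influences allocation or acceptance of the graft, while eligibility and MELD are established before randomisation.
4. Report every cancelled randomisation by arm and centre. The audit trail described in Sequence generation {16a} already records these events, so this can be done for patients randomised before any change.

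The cost is a wording amendment, two required fields and one table. If the change counts as substantial, the protocol's own route through the ethics committee and competent authority applies. The practical downside is shorter notice for setting up the device. Under Method of use of the device, it is needed only after transport in cold storage and back-table preparation, which leaves an interval after confirmed harvest; whether that is long enough is for each centre to confirm.

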#### Follow-up visits

Visits 3–11 (6 and 12 h (± 2 h) after reperfusion and postoperative days 1–7, ± 1 day):Laboratory analyses (AST, ALT, GGT, alkaline phosphatase, bilirubin, factor V, INR, platelets, creatinine, GFR, lactates) will be performed. Concomitant medications and adverse events will be collected.

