Recipient blood level of factor V at 6 h (± 2 h), 12 h (± 2 h) and every day until POD7Arterial lactates at 6 h (± 2 h), 12 h (± 2 h) and every day until discharge from intensive care (and maximum until POD7)MEAF score (0–10) at POD3, including POD3 bilirubin, ALT max, and INR max at POD3. This score will be compared with the Olthoff’s definition of EAD and the L-GrAFT risk factorL-GrAFT risk factor (− 6 to + 6) including AST, INR, total bilirubin, and platelets every day until POD 10. This score will be compared with both MEAF score and Olthoff’s scoreKidney function testsDaily serum creatinine level during the first 7 PODsDaily glomerular filtration rate (assessed using MDRD and CKD-EPI) during the first 7 PODsDifference between the two treatment arms in the proportion of patients requiring renal dialysis within the first 7 PODs90-day morbidity and mortalityDifference between the two treatment arms in the proportion of patients with severe postoperative complication (defined as Dindo–Clavien classification ≥ 3) occurring before day 90 post surgeryDifference in means between the two treatment arms of the comprehensive complication index (CCI) [19] at day 90Difference between the two treatment arms in the proportion of patients who were deceased before day 90 after surgeryDifference in means between the two treatment arms of the length of intermediate care unit stay and total hospital stayDifference between the two treatment arms in the proportion of patients with intra- and extrahepatic biliary complications within the first year after liver transplantation, assessed by:Serum cholestasis parameter (bilirubin, gamma*-*glutamyl transferase, alkaline phosphatase) every 3 months until 1 yearLiver contrast-enhanced MRI, including a magnetic resonance cholangiopancreatography (MRCP), 12 months after liver transplantation (except for patients who underwent a re-transplantation during the study)Actuarial graft and patient’s survival rates at 3 months and 1 yearDifference between the two treatment arms in the proportion of patients without graft loss at 3 months and 1 year.Difference between the two treatment arms in the proportion of patients alive at 3 months and 1 year.Costs of liver transplantation with ECD grafts using HOPE or not, incremental cost-effectiveness ratio at 12 months post-surgery. Details about the cost-effectiveness analysis are given in Supplementary Material 2.

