#### Visit 13 (3 months (± 30 days))

After liver transplantation, patients have regular checks at hospital, where physical examinations and lab test are performed (AST, ALT, GGT, alkaline phosphatase, bilirubin, factor V, INR, platelets, creatinine, GFR). During this appointment, the following will be recorded: the incidence of main postoperative complications (kidney function disorders, need for dialysis, infections, cholestasis and biliary obstructions, vascular complications, acute rejection, arterial or portal vein thrombosis, biliary fistula), Clavien–Dindo classification score, comprehensive complication index (CCI), reintervention, length of stay in intensive care unit, length of hospital stay, retransplantation, or death within 3 months after liver transplantation.

Adverse events and concomitant medications will be collected.

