##### Safety population (SAF)

This dataset includes all transplanted subjects for whom at least one follow-up safety data is available. This population will be used for safety analyses.

The primary population of interest will be the FAS.

Descriptive summary statistics for continuous variables will include the number of observations (*n*), mean, standard deviation (SD), median, minimum (min), maximum (max), and 25th and 75th percentiles (IQR). Descriptive summary statistics for categorical data will include frequency counts and percentages *N* (%). Percentage calculations will be based on the number of patients for whom there are no missing data.

The primary endpoint will be expressed as the total number of cases in each group and in percentages, with a 95% confidence interval. The categorical variables of the secondary endpoints will also be expressed as the total number of cases in each group and in percentages with a 95% confidence interval.

Categorical variables will be compared between the two study arms using the chi-squared test or the Fisher’s exact test, as appropriate. The continuous variables of the secondary endpoints will be compared using the Mann–Whitney *U* test.

In order to take into account the potential effects of confounders on the primary endpoint, univariate and multivariate logistic regressions will be performed.

90-day morbidity and mortality will be studied using a Kaplan–Meier analysis and comparison between groups will be performed using the log-rank test.

A *p*-value < 0.05 will be considered as statistically significant.

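### Daily creatinine and GFR to POD 7 are compared without the collected pre-transplant value and without a rule for values on dialysis: lost precision and possible attenuation in secondary endpoints

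*Protocol article*

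**What the plan says.** **Endpoints.** Under Kidney function tests, the Secondary endpoints section lists three items: daily "serum creatinine level during the first 7" postoperative days; daily GFR by MDRD and CKD-EPI over the same days; and the difference between arms "in the proportion of patients requiring renal dialysis within the first 7 PODs".

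**Analysis.** The text that closes the analysis-sets part of the Statistical methods states: "The continuous variables of the secondary endpoints will be compared using the Mann–Whitney" U test. Regression is provided for one endpoint only: "In order to take into account the potential effects of confounders on the primary endpoint, univariate and multivariate logistic regressions will be performed". No sentence brings a baseline value into a secondary comparison, and none says how creatinine or GFR measured on dialysis is treated.

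**Data held.** The D0 visit (V2) records creatinine, GFR and dialysis status (with MELD) before transplantation. The screening visit also pairs creatinine with dialysis: "The MELD score at inscription (INR, creatinine, bilirubin, and dialysis) is also recorded". The 6 h, 12 h and POD 1–7 visits repeat the laboratory panel, ending "platelets, creatinine, GFR, lactates) will be performed".

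**Fallback.** Section {20c} leaves missing or invalid secondary-endpoint data to the principal investigator and the person in charge of the analysis, who choose between treating them as missing and imputing. It gives no criterion.

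**The concern.** There are two separate issues, and they have different consequences.

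**Baseline.** Early creatinine after transplant depends partly on kidney function before it. Leaving out a value that is already recorded widens the interval around the treatment contrast. Randomization keeps the comparison unbiased.

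**Dialysis.** Dialysis removes creatinine, and both GFR formulas are computed from creatinine. A value taken on dialysis reflects treatment as well as kidney function. If such values are ranked like any others and one arm has more dialysis, that arm's creatinine looks better than its kidneys are. The contrast then moves toward no difference, whether HOPE helps or harms the kidney. At stake is how two secondary endpoints are read, not the trial's main conclusion.

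**Working it through.** **1. The plan's own figure.** The protocol gives no creatinine SD, dialysis rate or power for the kidney endpoints. Its only sample-size figure is for EAD, 30% versus 15%, two-sided alpha 0.05, power 0.80. With the arcsine effect size, h = 2·asin√0.30 − 2·asin√0.15 = 0.3639, and n = 2(1.960 + 0.842)²/h² = 118.55, so 119 per group. Then 119/0.90 = 132.2, so 133. Both figures reproduce; 119 per arm is used below.

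**2. Baseline adjustment.** For a pre/post correlation r, the variance factor is 1 − r² and the interval-width factor is its square root. The range of r is an assumption.
- r = 0.5: variance 0.75 (25% less); width 0.87 (13% less).
- r = 0.7: variance 0.51 (49% less); width 0.71 (29% less).

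**3. Values on dialysis, by simulation.** All inputs are assumptions: log-creatinine SD 0.5, control median 110 µmol/L, correlation with baseline 0.6, HOPE benefit 0.20 on the log scale, patients above a threshold dialysed, their creatinine then lowered by 20, 40 or 60%. There were 1,500 repetitions, with Mann–Whitney at 0.05. Power is shown with on-dialysis values ranked as measured, and in brackets on undistorted values:

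| Control-arm dialysis | 20% lowering | 40% lowering | 60% lowering |
|---|---|---|---|
| 5% | 0.845 (0.845) | 0.834 (0.837) | 0.799 (0.839) |
| 10% | 0.851 (0.851) | 0.845 (0.859) | 0.759 (0.865) |
| 20% | 0.833 (0.839) | 0.795 (0.843) | 0.603 (0.856) |

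- The mean log difference of 0.20 is observed as 0.171–0.196 at 5% dialysis, 0.151–0.189 at 10% and 0.116–0.179 at 20%.
- With no true effect, the rejection rate using measured values is 0.038–0.058, so no false difference is created.
- Worst rank for dialysed patients gives power 0.83–0.86. Adding the baseline value gives 0.94–0.96. Dialysis here depends strictly on creatinine, which favours worst-rank scoring.
- Fisher's test on the dialysis proportion has power 0.11–0.45.

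**4. Where a dialysed patient lands in the ranking.** At 10% control dialysis the threshold is 110 × exp(0.5 × 1.282) ≈ 209 µmol/L. Lowered by 40% this is about 125, still above the median of 110. Lowered by 60% it is about 84, below the median.

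**5. Rank-scale check with other assumed inputs.** Take 15% versus 8% dialysed, non-dialysed creatinine log-normal with mean 130 and log SD 0.3–0.5, identical in both arms, and dialysed patients reading a single value x. The rank effect is 0.07·F(x) − 0.035, where F is the non-dialysed distribution. Under worst-rank scoring it is 0.035, so the fraction retained is 2F(x) − 1.
- x = 150: F = 0.70–0.73, so 41–47% retained.
- x = 220: F = 0.90–0.97, so 81–94% retained.

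This concerns only the part of the contrast that arises from dialysed patients. Again, the loss is large only when the lowering is strong.

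**The case against.** **Dialysis is not disregarded.** It is a between-arm endpoint in the same item over the same 7 days, so an excess in one arm would be reported beside creatinine and GFR. This stands, and it rules out saying that dialysis is ignored. It does not repair the creatinine contrast, and its low power above means it cannot stand in for a rule.

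**The detail may sit in an analysis plan that is not shown.** This is fair for the dialysis rule: that on-dialysis values are ranked like any others is inferred from silence. But the article does fix an unadjusted test for all continuous secondary endpoints and keeps regression for the primary one. The only fallback it states, section {20c}, has no criterion.

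**A reader might infer that daily dialysis status is not captured**, because the POD 1–7 visits name only laboratory tests, while "kidney function disorders, need for dialysis" appears at the 3-month visit. The documents do not support this. The case report form is in a supplement that is not shown, adverse events are collected at the early visits, and the 7-day dialysis endpoint already needs this information.

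**A reader might infer that the missing baseline biases the result.** It does not. Stratification at MELD 30, with creatinine and dialysis among the score's listed components, also limits gross imbalance. Only precision is lost.

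**Conclusion.** The point holds in a limited form. The stated test leaves out baseline kidney values already collected, at a cost in precision (25–49% of variance if the correlation is 0.5–0.7). The article also gives no rule to protect creatinine and GFR from values altered by dialysis. If dialysis rates differ between arms, the contrast may be attenuated: mostly modestly at 5–10% control-arm dialysis (largest power loss 0.865 to 0.759) and more with frequent dialysis and strong lowering (0.856 to 0.603). Every driving figure is an assumption, because the documents give no dialysis rate, creatinine SD or size of lowering.

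Two stronger readings are not supported. One is that the sickest kidneys score as improved: in most scenarios dialysed patients still rank worse than the typical patient, only less so than they should. The other is that a kidney benefit of HOPE is hidden. A calculation on means can suggest it: with 15% versus 8% dialysed, 350 untreated, 150–220 on dialysis and 130 otherwise, a true 0.07 × 220 = 15.4 µmol/L shows as 0.07 × (20 to 90) = 1.4–6.3, or 9–41%. But the planned test is on ranks, where the same inputs retain more (step 5), and those inputs are not in the documents.

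This is minor. The primary endpoint and sample size are unaffected.

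**What to change.** In the Statistical methods:

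1. Analyse creatinine and GFR adjusted for the V2 value, by rank-based or log-scale ANCOVA.
2. Give patient-days on or after the start of dialysis the worst rank, at least as a pre-specified sensitivity analysis, using the dialysis data already needed for the 7-day endpoint.
3. Report the 7-day dialysis endpoint also in patients not dialysed at V2. The listed exclusions do not remove patients dialysed before transplant, and V2 records that status.

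The cost is a few sentences of analysis text, with no change to recruitment or to the primary analysis. The downside is that worst-rank results are rank effects rather than mean differences, so descriptive creatinine and GFR summaries should still be shown, with the number of patients on dialysis each day.
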